### MRI data

Functional imaging data collected during the motor tasks will be retrospectively motion corrected with a slice-based second-order motion model [45,46] in parallel with physiologic noise regression [47], spatially filtered [48] and analyzed for task-related activation using a least-squares fit of the voxel-level BOLD signal to a reference function generated from the task design [49]. The result will be a whole brain map of Student’s t-values reflecting the response of each voxel for each task. A paired *t*-test of the total volume of activation above a t-value of 3.5 (p < 0.001, uncorrected) in the supplemental motor area will be calculated in all subjects. Correlation will be calculated between the change in activation volume of the supplemental motor area and subcortical structures of interest (globus pallidus, putamen, and thalamus) for each subject and the corresponding biomechanical measures during a finger tapping task during the scan and UPDRS rating.

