Previous studies suggests that exercise interventions must be intense and continuous to elicit benefits on PD symptoms [6,16]. However, individuals with PD typically experience varying levels of rigidity and bradykinesia, which may limit their ability to complete continuous, high-intensity exercise [17-19]. To address these issues, a novel mode of aerobic exercise termed forced exercise (FE) was developed to aid individuals with neurological deficits to achieve and maintain a high cadence pedaling rate. Initially, the FE paradigm was implemented using a tandem stationary cycle where the trainer on the front of the tandem bicycle pedaled between 80-90 rpms, and the individual with PD on the back of the bike was forced to pedal at the same rate due to the pedals on a tandem bike being mechanically linked by the bike chain [20,21]. In a preliminary study completed by [name] and colleagues, motor outcomes were examined after individuals with PD completed 8 weeks of cycling using either the FE approach or voluntary exercise (VE), where individuals cycled on a stationary bike at a self-selected cadence [20,21]. The Unified Parkinson’s Disease Rating Scale (UPDRS) [22] motor subscale score for individuals randomized into the FE group improved 41% for rigidity, 38% for tremor, and 28% for bradykinesia. Additionally, biomechanical analysis of grasping force and torque indicated that FE, but not VE, resulted in an improvement in the coordination and control of grip and load forces during the performance of a bimanual object manipulation task [20,21]. Functional connectivity magnetic resonance imaging (fcMRI) was conducted during the following conditions: 1) on PD medication, 2) off PD medication, and 3) off medication after a single bout of FE. Results demonstrated that FE and PD medication produce similar brain connectivity responses, and likely share similar underlying mechanisms [23]. An improvement in upper extremity motor control processes following a lower extremity exercise intervention coupled with the change in fcMRI indicate that FE is altering brain structure and potentially function in some manner. However, the specific mechanism and identification of the phenotype of PD patients that could benefit from FE is unknown.

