### MRI data collection

For this study, structural MRI, functional MRI (fMRI), fcMRI and cerebral blood flow (CBF) data will be acquired on four occasions: Baseline (on and off antiparkinsonian medication), EOT, and EOT + 4 weeks. The structural scan is a T1-weighted anatomic image for identifying brain anatomy. The fMRI and fcMRI scans will be acquired with blood oxygen level-dependent (BOLD)-weighted echoplanar imaging scans. Two fcMRI scans will be acquired while subjects rest in the scanner with eyes closed. Two fMRI scans will be acquired in each session while subjects complete finger tapping in the following self-paced repeating sequence: digit 1, digit 3, digit 5, digit 2, digit 4 with each limb (left and right limbs, in random order) in a block paradigm (alternating 48 second-long blocks of tap and rest phases, repeated 4.5 times) to determine the relationship between changes in upper extremity motor performance and pattern of brain activation. Additional measures recorded for exploratory purposes include fcMRI between nodes of the putative motor network.

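### The SMA activation volume depends on residual scan noise and on self-paced tapping as well as on the BOLD response, so a rise after forced exercise could not be read as a changed response

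*Protocol article*

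**What the plan says.** All of this is in the protocol article.

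- **How the t-value arises (MRI data).** Task activation comes from "a least-squares fit of the voxel-level BOLD signal to a reference function generated from the task design", which gives a t-value for each voxel.
- **The measure (MRI data).** A paired t-test is planned on the "total volume of activation above a t-value of 3.5 (p < 0.001, uncorrected) in the supplemental motor area".
- **The task (MRI data collection).** Scans are acquired "while subjects complete finger tapping in the following self-paced repeating sequence", in a block design of "alternating 48 second-long blocks of tap and rest phases, repeated 4.5 times". The stated purpose is to link change in upper-limb performance to brain activation.
- **Safeguards (MRI data).** The data are "retrospectively motion corrected with a slice-based second-order motion model", with physiologic noise regression and spatial filtering, before the fit.
- **Use of tapping data (MRI data).** Change in activation volume, in the SMA and in the globus pallidus, putamen and thalamus, is correlated with in-scan tapping measures and with UPDRS.
- **Recognised confounder (Arterial spin labeling data and CBF measurement).** Basal blood flow is measured because it alters BOLD amplitude. It may be included in a population analysis.
- **Hypothesis (Background).** FE is expected to increase activation; voluntary exercise and control are expected to show no change.
- **Expected motor change (Background).** In the preliminary study, UPDRS motor ratings with FE "improved 41% for rigidity, 38% for tremor, and 28% for bradykinesia".

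**The concern.** A count of voxels above a fixed t-value is not a pure measure of response, because the noise of each scan sits in the denominator of every t. A participant who lies more steadily at the second scan can show a larger activated volume with the same BOLD response. The block reference function also carries no information on how fast the participant tapped, so any effect of tapping rate on the signal is counted as activation.

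This matters more here than in most trials because the treatment is meant to improve tremor and bradykinesia, and all follow-up scans are off medication. If FE steadies participants or speeds their tapping, the volume could rise in the FE arm in particular and in the hypothesised direction. Randomisation does not protect against this, since the difference arises after treatment starts. At stake is the reading of Aim 3: whether FE changed the neural response, or participants performed the same task more steadily or faster.

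**Working it through.** **Step 1: the plan's own figure.** The article pairs t = 3.5 with p < 0.001. The task lasts 4.5 × (48 + 48) s = 432 s. The repetition time of the fMRI scans is not given; assuming 1.5 to 4 s gives 288 to 108 volumes. Allowing for 2 model terms, with or without 20 further nuisance terms, the degrees of freedom run from 286 down to 86. The two-sided p at t = 3.5 is then 0.0005 to 0.0007, and the one-sided p 0.0003 to 0.0004. The label is correct.

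**Step 2: what moves the volume.** For each voxel t = b / (σ·c), where b is the fitted amplitude, σ the residual SD and c a constant of the design. If noise falls by a fraction r and the response is unchanged, the expected t is multiplied by k = 1/(1 − r). A rise in amplitude by a fraction a gives k = 1 + a. Both enter only through k, so a 10% fall in noise (k = 1.111) has the same expected effect on the volume as an 11.1% rise in response. This is algebra and needs no assumption about the trial.

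**Step 3: illustrative size.** Assume the true (noise-free) voxel t-values in the SMA are Normal with mean μ and SD s, and that each observed t adds sampling error of variance 1. The share of voxels above threshold is

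P(k) = 1 − Φ[(3.5 − kμ) / √((ks)² + 1)].

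For μ = 3, s = 1.5:
- no change: (3.5 − 3)/√(2.25 + 1) = 0.277, so P = 0.391;
- 10% less noise: (3.5 − 3.333)/√(2.778 + 1) = 0.086, so P = 0.466;
- ratio 0.466/0.391 = 1.19, a 19% larger volume.

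| μ | s | Share at baseline | 10% less noise | 20% less noise | 10% more noise |
|---|---|---|---|---|---|
| 2 | 1.5 | 0.203 | +26% | +57% | −21% |
| 3 | 1.5 | 0.391 | +19% | +40% | −17% |
| 4 | 1.5 | 0.609 | +13% | +25% | −13% |
| 3 | 1 | 0.362 | +26% | +55% | −22% |
| 3 | 2 | 0.412 | +15% | +31% | −14% |

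Over these settings a 10% fall gives +13% to +26%. Crossing the extreme values of μ and s widens this to +11% to +36%.

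**Step 4: would the paired t-test pick it up?** A simulation used μ = 3, s = 1.5, 300 voxels, 30% variation between participants, 20% variation between sessions, 40 participants and 400 runs per setting, with no change in response. A significant increase appeared in about 3% of runs with no noise change, in 58% with a 10% fall in noise, and in essentially all with a 20% fall.

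**Step 5: tapping rate.** The article gives no tapping rate and no relation between rate and SMA signal, so no size can be put on this part. The structural point is that the reference function is built from tap and rest blocks, and rate is not stated as a term in the paired test.

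**The case against.** The case on the other side is substantial.

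- **Noise is not ignored.** A reader might infer that the plan guards against blood flow but not against noise. That is wrong: motion correction, physiologic noise regression and spatial filtering are all stated. What remains is narrower. These steps lower residual variance but do not equalise it between sessions, which a fixed t threshold would need.
- **Task performance is a variable of interest.** Tapping is measured in the scanner, and its correlation with volume change is planned. This stands as a real merit, since it would expose a performance-linked change. It would not say which explanation holds, because steadier or faster tapping could itself produce the correlation.
- **Volume fits the hypothesis.** The Background hypothesis concerns the extent of activation as well as its pattern, and volume measures extent. If faster tapping makes the SMA more active, that is more activation in a real sense. This stands, and is why the volume should be kept.
- **Key links are assumed.** The article does not say that limb tremor drives residual scan noise or that faster tapping raises SMA signal. The preliminary improvements are UPDRS ratings after tandem cycling, not in-scan measures. This stands; the mechanism is plausible but undocumented.
- **Adjustment for tapping rate can mislead.** Rate is a post-randomisation variable and may be a consequence of the neural change. A rule that a change counts as neural only if it survives adjustment could remove a real effect. This stands.
- **The article is condensed.** A fuller imaging plan may hold more covariates, and a population analysis is mentioned. That may be so, but the activation measure and its test are stated here and can be judged as stated.

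**Conclusion.** The point holds as a caution on what the measure can show. The SMA volume depends on residual noise by construction, the task is self-paced, and neither residual noise nor tapping rate is stated as a term in the comparison. A rise in volume after FE could therefore occur without a changed response, in the hypothesised direction.

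The dependence on noise is certain; its size in this trial is unknown. The figure of roughly 13% to 26% for a 10% fall in noise rests on assumed voxel t distributions and an assumed noise change. Neither is in the document.

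A reader might go further and conclude that a tremor or motor improvement would be reported as increased activation. The document does not support that: it shows that this could happen, not that it will. Nor is the t = 3.5 threshold mislabelled. The consequence is confined to the interpretation of Aim 3. The primary outcome, UPDRS motor score, does not depend on it.

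**What to change.** 1. Analyse the mean regression coefficient or percent BOLD signal change in anatomically defined SMA, globus pallidus, putamen and thalamus regions, using the same regions at every scan. Report it alongside the volume above t = 3.5, which is kept as the measure of extent.
2. Report in-scan tapping rate and residual motion by arm and visit.
3. Repeat the comparison with the in-scan tapping rate included, labelled as a sensitivity analysis. Do not make it a condition for calling a change neural, since tapping rate may mediate the effect.
4. State the limit of the first step: noise then affects the precision of signal change rather than its expected value, but any dependence on tapping rate remains.

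The cost is reanalysis of BOLD scans and tapping measures that are already planned, with no added scans or visits. The downside is small: regional amplitude is less sensitive to a purely spatial spread of activation, which is why the volume stays in the report.

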The *Cyc*lical *L*ower Extremity *E*xercise for Parkinson’s (CYCLE) Trial is designed to test the hypothesis that FE and VE, while both aerobic, produce different clinical outcomes as a result of differential effects on the CNS. Specifically, the aims of the CYCLE trial are: 1) To determine the effects of FE and VE on motor function in individuals with PD; 2) To determine the effects of FE and VE on non-motor function in individuals with PD; and 3) To determine the pattern of magnetic resonance imaging (MRI) activation associated with FE and VE. It is hypothesized that FE will elicit significantly greater improvements in clinical and biomechanical measures of motor and non-motor performance when compared to voluntary and no-exercise control groups. Further, it is hypothesized that FE will elicit increased cerebral blood flow and cortical and subcortical activation following exercise, while voluntary and no-exercise groups will result in no change in the pattern or extent of activation as seen on neuroimaging.

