### Data analysis

Participants in all three groups will be compared descriptively on potentially confounding baseline variables (i.e., age, disease severity, and levodopa equivalent daily dose (LEDD)) to assess the extent of any imbalance across groups. Baseline variables in which there appears to be a clinically important baseline difference, or in which the standardized difference (absolute value of difference in means divided by pooled SD) between any 2 groups is greater than 10% will be included as covariates. P-values from these baseline variable comparisons will not be used to determine the need for covariate adjustment, as that criterion can be misleading.

The FE, VE, and the no-exercise control groups will be compared on each outcome of interest (motor, non-motor) using repeated measures analysis of covariance. For motor and non-motor outcomes, groups will be compared on outcomes at the mid-treatment, EOT, EOT + 4 weeks, and EOT + 8 weeks adjusting for the baseline (on and off medication) period as a covariate. The effects of group, time, and the group-by-time interaction will be assessed for each outcome. In the case of a significant interaction, the groups will be compared at each time point. Tukey’s correction for multiple comparisons will be used. Data will be transformed as needed to meet model assumptions. In addition to p-values, the estimated treatment effect and its 95% CI will be of interest as these data will aid in formulating exercise recommendations and potential benefits. For each hypothesis, significance level will be set at 0.05. Each participant’s change in fitness based on change in peak VO_2_ from CPX testing will be used as a covariate. This will remove the effect of possible differences in improvement in fitness level across the groups from confounding the results. Correlation between LEDD and the time spent within target HR zone during training, amount of work performed, and change in primary outcome variables in motor and non-motor outcomes will be assessed. If the LEDD is significantly correlated with these outcomes, it will be included as a covariate in the related analysis.

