### Arterial spin labeling data and CBF measurement

Exercise may have an effect on baseline CBF. Basal CBF will affect the amplitude of the BOLD signal in response to a given neuronal activation level. In order to control for this possible confound to our measurement, we will measure basal CBF during each imaging session in order to 1) assess whether there are observed baseline CBF changes with the proposed exercise regimen, and 2) to permit the inclusion of this measure in a population analysis in order to control for this effect. A Q2TIPS arterial spin labeling (ASL) scan will be used to measure baseline CBF [50]. The ASL scan parameters are as follows: TE/TR/Flip = 2300/13/80, 12 axial slices 5mm thick, 1mm slice gap, FOV = 256x256, matrix = 64x64, TI1/TI2/SST = 700/1400/1100, bandwidth = 150kHz, repetitions = 139, Tag Slab = 100mm with 25mm gap.

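### The only significance test named for supplemental motor area activation volume is a paired t-test with no group term, which does not match the between-group contrast that is hypothesised and powered

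*Protocol article*

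**What the plan says.** The Background section of the protocol article sets out the contrast to be shown. The two forms of exercise are expected to "produce different clinical outcomes as a result of differential effects on the CNS", and for imaging the hypothesis is that "FE will elicit increased cerebral blood flow and cortical and subcortical activation following exercise, while voluntary and no-exercise groups will result in no change".

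The Power analysis section says no published data exist for Aims 2 and 3. It then gives a general figure: 99% power for a 1.2 SD difference between groups with 40 per exercise group. It adds that every calculation assumes a Tukey adjustment for three groups.

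The MRI data section names a paired t-test, with the "total volume of activation above a t-value of 3.5 (p < 0.001, uncorrected) in the supplemental motor area will be calculated in all subjects". The other analysis of activation volume there is correlational: "Correlation will be calculated between the change in activation volume of the supplemental motor area and subcortical structures of interest" and the finger-tapping biomechanics and UPDRS rating.

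The three-group model is in the Data analysis section, where the groups "will be compared on each outcome of interest (motor, non-motor) using repeated measures analysis of covariance". MRI is not in that list.

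The MRI data collection section lists four scan occasions: baseline on medication, baseline off medication, EOT, and EOT + 4 weeks.

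**The concern.** The question concerns a difference between randomised groups, but the named test looks only at change within subjects. *In all subjects* can be read in two ways, and neither gives a group contrast.

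- **Pooled over all arms.** A significant result says that volume differed between two scans on average. Practice at the tapping task, scanner drift or time would produce it as readily as exercise would.
- **Run in each arm.** The result is a set of separate p-values. Significant in one arm and not in another is not a test of the difference between them. A non-significant result also does not establish the predicted "voluntary and no-exercise groups will result in no change in the pattern or extent of activation as seen on neuroimaging".

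A third gap is that the pair is not named. With four occasions, the test could compare baseline with EOT, baseline with EOT + 4 weeks, or on with off medication at baseline.

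At stake is whether the SMA activation result can support a statement about FE against VE or control. The randomised arms needed for that statement are already in the design.

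**Working it through.** **Inputs.** From the article: 100 participants randomised 2:2:1, hence 40 FE, 40 VE and 20 control; significance level 0.05; 1.2 SD and 99% power; Tukey adjustment for three groups. Assumed: two-sided tests, all participants scanned, and mean changes in units of the SD of change. The article gives no effect size for change in MRI outcomes, so a range is shown.

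**1. The plan's own power figure.** With 97 error degrees of freedom, the Tukey critical value is q(0.95; 3, 97)/√2 = 2.380. For FE against VE at 1.2 SD, the noncentrality is 1.2/√(1/40 + 1/40) = 5.37 and power is 99.8%. The stated 99% is therefore met, but by a between-group comparison, which is not the test in the MRI data section.

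**2. Scope of the three-group model.** Besides being limited to motor and non-motor outcomes, it is set at mid-treatment, EOT, EOT + 4 weeks and EOT + 8 weeks. Table 1 shows no MRI at mid-treatment or EOT + 8 weeks. The model was not written for imaging.

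**3. Pooled reading (n = 100).**
- Equal change of 0.30 SD in every arm: noncentrality 0.30 × √100 = 3.0 on 99 degrees of freedom, and the test rejects with probability 0.844. In a simulation of 20,000 trials it rejected in 85%, while a between-group F test rejected in 5%.
- Change δ in FE only: pooled mean change = (40δ + 40×0 + 20×0)/100 = 0.4δ.
- FE +0.5, VE −0.5, control 0: pooled mean = (40×0.5 − 40×0.5 + 0)/100 = 0. In simulation the pooled test rejected in 3% and the F test in 98%.

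Dilution is a fault of estimation and attribution more than of power. With FE +0.5 and no change elsewhere, the simulated pooled test rejected in 49%, against 57% for the F test and 45% for the Tukey FE–VE contrast. The main trouble is that a rejection cannot be attributed to FE.

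**4. Arm-by-arm reading, equal true change d in every arm.** Power of each paired test comes from the noncentral t with noncentrality d√n and n − 1 degrees of freedom. The arms are independent, so P(FE significant, VE not) = p40(1 − p40) and P(FE significant, control not) = p40(1 − p20).

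| d (SD) | p40 | p20 | FE yes, VE no | FE yes, control no |
|---|---|---|---|---|
| 0.20 | 0.235 | 0.136 | 18% | 20% |
| 0.30 | 0.457 | 0.247 | 25% | 34% |
| 0.40 | 0.694 | 0.397 | 21% | 42% |
| 0.45 | 0.793 | 0.480 | 16% | 41% |
| 0.60 | 0.959 | 0.721 | 4% | 27% |
| 0.80 | 0.9985 | 0.924 | 0.1% | 8% |

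For example, at 0.45 SD, 0.793 × (1 − 0.793) = 0.164 and 0.793 × (1 − 0.480) = 0.412. The last column is larger because the control arm is half the size of the FE arm. The full predicted pattern, FE significant with both other arms not, arose in 19% of simulated trials at 0.30 SD and 5% at 0.50 SD, although the arms did not differ.

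**5. A group comparison on the same data.** The F test rejects in about 5% when all arms change equally. At 1.2 SD, Tukey-adjusted power is 99.8% for FE–VE and 97.6% for FE–control (40 against 20). The FE–VE difference detectable with 90% power is (2.380 + 1.282) × √(2/40) = 0.82 SD.

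**The case against.** The strongest reply is that the article is a condensed account. The MRI data section never calls the paired t-test the sole or confirmatory analysis. The power statement shows that a comparison of groups was contemplated. The Testing and outcome measures section says MRI results will be compared at time points. The arterial spin labeling section measures blood flow "to permit the inclusion of this measure in a population analysis in order to control for this effect". A fuller plan may hold a group model.

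Part of this stands. A missing second-level imaging model would not be a fault in an article. But the article does fix one test, and that test does not match its own hypothesis and power statement. Neither of the two general remarks on MRI names a group contrast.

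Two further objections are fair. Aim 3 itself is worded as determining a pattern, and its hypothesis is literally a set of arm-specific changes, so the between-group reading is an interpretation. It is well supported by the contrast drawn in that sentence, by the overall hypothesis of differential effects and by the three-group power statement. And the SD values in the table are assumptions: at 1.2 SD the false contrast almost vanishes (about 0% for VE, 0.1% for control). The only SD-scale figures in the article, 1.2 and 1.3, describe between-group differences, so they do not settle how large a common within-arm change might be.

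**Conclusion.** The point holds for SMA activation volume. The named test has no group term and an unnamed pair, so neither reading of it can show that FE differs from VE or control. The pooled figure (about 84% rejection under an equal 0.30 SD change) and the arm-by-arm ranges (about 0 to 25% against VE, 8 to 42% against control, for 0.2 to 0.8 SD) rest on assumed changes, two-sided 0.05 tests and complete scans.

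A reader might infer more than the document supports:

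- **That Aim 3 as a whole cannot be answered.** The aim also covers cerebral blood flow and subcortical activation, and blood flow change is assessed separately. The fault lies in one test.
- **That the test is certainly pre/post.** The pair is not stated. A baseline on–off medication comparison is possible, and it would not test exercise at all.
- **That a spurious FE-against-control contrast is likely from sample size alone.** The probability peaks at about 42% and is small for large changes.
- **That the trial's main result is at risk.** The primary outcome is the UPDRS motor score, which has a three-group model.

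Severity is moderate.

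**What to change.** In the MRI data section, state that the exercise effect on SMA activation volume is tested by analysis of covariance of off-medication volume on randomised group, with off-medication baseline volume as covariate. A repeated-measures model covering EOT and EOT + 4 weeks would serve equally. Report the three pairwise differences (FE–VE, FE–control, VE–control), Tukey-adjusted, with 95% confidence intervals. This agrees with the adjustment already assumed in the Power analysis section.

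Name the scans that enter each comparison. If the paired t-test was meant for on against off medication at baseline, say so and keep it under that label. Otherwise keep within-arm paired changes as descriptive estimates with confidence intervals, and judge the expected absence of change in VE and control from those intervals rather than from non-significance.

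The cost is analysis wording only. The scans, visits and sample size stay as they are.

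### The activation tests stated for Aim 3 do not match its hypothesis: one paired test in the supplemental motor area that compares no groups, and only a correlation for the subcortical regions

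*Protocol article*

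**What the plan says.** Aim 3 in the Background of the protocol article is "To determine the pattern of magnetic resonance imaging (MRI) activation associated with FE and VE". The hypothesis attached to it has a direction and a contrast between arms. For the forced-exercise arm, "it is hypothesized that FE will elicit increased cerebral blood flow and cortical and subcortical activation following exercise". For the two comparison arms the same sentence predicts stability: "while voluntary and no-exercise groups will result in no change in the pattern or extent of activation as seen on neuroimaging".

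The MRI data section then states two analyses of task activation:

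- **A test.** It is a paired "test of the total volume of activation above a t-value of 3.5 (p < 0.001, uncorrected"), and it is located "in the supplemental motor area will be calculated in all subjects".
- **A correlation.** "Correlation will be calculated between the change in activation volume of the supplemental motor area and subcortical structures of interest (globus pallidus, putamen, and thalamus") on one side; finger-tapping measures during the scan and the UPDRS rating on the other.

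The Data analysis section applies its repeated measures analysis of covariance to motor and non-motor outcomes and does not name MRI outcomes. The Power analysis section covers Aim 3 only through a general figure: 99% power for a difference of 1.2 SD between exercise groups of 40, with Tukey adjustment for three groups.

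**The concern.** The hypothesis makes a statement about mean change, by arm, in cortical and subcortical regions. Neither stated analysis answers it.

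The paired test asks whether activation volume in one region changed from one scan to another. It has no group term, so it cannot separate an effect of FE from one shared by all arms, such as practice at the tapping task or familiarity with the scanner.

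The correlation asks whether subjects who changed more in one measure also changed more in another. That is a different question from whether activation rose.

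If only these two analyses are run, Aim 3 can yield a result in the supplemental motor area that is not attributable to FE, and a subcortical result that does not speak to the hypothesised increase. The group contrast and the choice of region would then be settled after the data are seen.

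**Working it through.** **1. Hypothesis against stated analysis**

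| Element of the hypothesis (Background) | Stated analysis (MRI data) |
|---|---|
| Cortical activation rises with FE | Paired t-test in one cortical region, the supplemental motor area |
| Subcortical activation rises with FE | No test of change; correlation only |
| VE and no-exercise groups do not change | No group comparison in any region |

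Three other places could fill the gap:
- The covariance analysis is limited to motor and non-motor outcomes.
- The whole-brain t-map records each voxel's response to each task. It is not a test of change or of groups.
- The arterial spin labeling section concerns basal blood flow. It mentions a population-level analysis in which blood flow would be a control variable, but does not describe that analysis.

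**2. What the paired test can show.** With 2:2:1 allocation and 100 participants, the arms are 40, 40 and 20. Suppose FE changes by δ and the other arms by 0. The pooled mean change is (40δ + 40·0 + 20·0)/100 = 0.4δ. A change of 0.4δ in every arm gives the same pooled mean, so the mean that the test examines is the same under the hypothesised pattern and under no group difference. Running the test within each arm would not repair this: significance in one arm and not in another is not a test of the difference between them.

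**3. What the correlation can show.** For change scores X and any constant c, corr(X + c, Y) = corr(X, Y). A uniform subcortical rise is therefore invisible to it, and a strong correlation can occur with zero mean change.

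For scale, take the 80 exercisers with no link between activation and UPDRS within an arm. Let FE exceed VE by d SD in activation and e SD in UPDRS improvement. Then r = (d·e/4)/√[(1 + d²/4)(1 + e²/4)].
- If UPDRS does not differ by arm, e = 0 and r = 0, so significance occurs in about 5% of trials.
- With the planning values, e = 5.0/8.0 = 0.625. For an assumed d = 0.85, r = 0.1328/√(1.181 × 1.098) = 0.117. Fisher's z gives 0.117 × √77 = 1.03 and a power of 18%. For d = 0.9, r = 0.122 and the power is 19%.

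In the second case the signal comes only from both means differing by arm. The d values are assumptions, not figures from the article.

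**4. The plan's own power figure.** Noncentral t with the studentized range for three groups, 97 df, 40 v 40, 1.2 SD: critical value 2.380, power 99.84%. The stated 99% reproduces and is not in dispute. It describes a comparison between groups, which the MRI data section does not contain.

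**5. Cost of sharing alpha over four regions.** The worst case under Holm is the Bonferroni level, 0.05/4 = 0.0125 (Tukey critical value 2.906). At 1.2 SD:

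| Contrast | Power at 0.05 | Power at 0.0125 |
|---|---|---|
| FE v VE (40 v 40) | 99.8% | 99.2% |
| FE v control (40 v 20) | 97.6% | 92.7% |

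For smaller assumed effects, a simple two-sample t-test (40 v 40, no Tukey) gives 94.2% and 84.3% at 0.8 SD, and 97.8% and 92.6% at 0.9 SD. These are illustrations that assume a usable scan pair from every participant; they are not properties of any test the article states. With no adjustment at all, four independent tests at 0.05 would carry a familywise error of 1 − 0.95⁴ = 18.5%.

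**The case against.** The strongest reply is that this is a condensed article. It does not say that the supplemental motor area is the only region to be tested, and its reference to a population-level analysis shows that the MRI data section is not the whole imaging plan. A list of tests by region is commonly left to a statistical analysis plan. A reader might infer that the subcortical increase will never be tested; the documents do not support that, because a test may exist in a plan that is not shown. What remains is that the article is not merely silent. It names a test, fixes its region, and gives the subcortical structures a separate use, and these choices do not match its own hypothesis.

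Second, the correlation has a purpose of its own. The MRI data collection section says the tapping scans are meant to relate change in upper-extremity performance to the pattern of activation, and the correlation does that. It is therefore not a misplaced analysis and should stay. It still does not test the increase.

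Third, a reader might infer that the supplemental motor area test is sound and need only be repeated in three more regions. That would give three more paired tests without a group contrast, so the repair has to change the test as well as the regions.

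Fourth, the consequence is limited. Aim 3 is the third, mechanistic aim, and nothing here affects the primary UPDRS comparison, the sample size or safety. This stands and sets the grade of the point.

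**Conclusion.** The mismatch is real in the current text. The hypothesis concerns cortical and subcortical activation and a contrast between arms; the stated test covers one cortical region with no contrast, and the subcortical regions have no stated test of change. It is a worthwhile, inexpensive correction rather than a threat to the trial's main result.

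The conclusion rests on comparing the sections and on two properties that hold at any effect size: a test of change without a group term compares no groups, and a correlation is unaffected by a constant shift. It does not rest on the power illustrations. In particular, the 5% chance of a significant correlation applies only if UPDRS does not differ by arm; with the planning values it is about 18–19%.

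**What to change.** In the MRI data section, replace the paired t-test with a comparison of activation volume at EOT between FE, VE and control, adjusted for the off-medication baseline, in the supplemental motor area, globus pallidus, putamen and thalamus. Apply Holm adjustment over the four regions and keep the three-group Tukey adjustment that the power calculation assumes. Retain the correlations as secondary analyses serving the purpose given under MRI data collection.

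Alternatively, restrict the activation hypothesis in the Background to the supplemental motor area, still with a group comparison, and label the subcortical analyses exploratory.

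If the population-level analysis mentioned in the arterial spin labeling section is already meant to supply these comparisons, describing it would resolve the point.

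No new scans are needed, because the planned correlation already requires each subject's change in volume in all four regions. The cost of the first option is that the supplemental motor area shares its alpha with three other regions: at 1.2 SD, at most about 0.6 percentage points of power for FE versus VE and 5 for FE versus control, and more at smaller effects. The second option avoids this loss but gives up a confirmatory answer on the subcortical part of the hypothesis.
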